### Inclusion criteria

Study participants will need to be: (a) women aged 18 or over registered with Playgroup WA Inc.; b) have a child between 0 to 5 years; (c) healthy to the extent that participation in a low-stress physical activity program would not place them at risk; (d) not taken part in any research that involves physical activity or nutrition within the last five years; and (e) not on a special diet.

### Sample size determination

In order to detect a 20% difference in physical activity at 80% power and 5% level of significance, sample size of 310 mothers of young children are required at the 6-months post-intervention survey in each of the intervention and control groups. A small effect size (0.2) [37] is assumed for studies on behavioural effects due to the influence of extraneous variables and the subtleties of human performance. Allowing for an attrition rate of 30%, 900 mothers of young children will be recruited into the study. Sample size calculations were determined using Power Analysis and Sample Size software [38].

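### The 310 per group matches an undeclared one-sided 5% test; read as two-sided, power for the 0.2 effect is about 70%, and the 20% target is not tied to that effect

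*Protocol article*

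**What the plan says.** Under Sample size determination, the protocol article sets its goal as to "detect a 20% difference in physical activity" and states that, "at 80% power and 5% level of significance, sample size of 310 mothers of young children are required", counted in each group at the six-month survey. The next sentence supplies the effect: "A small effect size (0.2) [37] is assumed for studies on behavioural effects". The section then allows for 30% attrition and arrives at 900 recruited, 450 per group.

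The section does not say whether the 5% is one-sided or two-sided. It does not say what the 20% is a percentage of, or whether it refers to a mean or a proportion. No mean, SD or baseline rate is given. The Statistical analysis section names multi-level repeated measures and logistic regression and mentions no one-sided hypothesis. The Study aim section speaks of evaluating the effect of the programme.

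**The concern.** There are two difficulties in the same paragraph.

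First, a 5% level given without qualification is ordinarily read as two-sided. On that reading the stated inputs do not lead to 310 per group, and the claimed 80% power is not reached. The chance of missing a true 0.2 SD effect would be about 30% rather than 20%, and a null result would be judged against a power the trial does not have.

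Second, the paragraph gives its target twice, as a 20% difference and as an effect size of 0.2, with nothing to connect them. A percentage difference and a standardised difference are different quantities. Without the connecting figures, a reader cannot tell how large a change in physical activity the trial was sized to detect.

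**Working it through.** **Inputs from Sample size determination:** standardised effect d = 0.2; power 80% (z = 0.8416); level 5% (z = 1.6449 one-sided, 1.9600 two-sided); 310 per group at six months; attrition 30%. Allocation is 450 to 450 (Abstract). Participants are treated as independent throughout.

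**1. Reproducing the 310.** For a comparison of two means, n per group = 2(z_level + z_power)² / d².
- One-sided 5%: 2 × (1.6449 + 0.8416)² / 0.04 = 309.1. With the t distribution it is 309.8, so **310**, with power 80.0%. This equals the article's figure.
- Two-sided 5%: 2 × (1.9600 + 0.8416)² / 0.04 = 392.4. With the t distribution it is 393.4, so **394**. The planned 310 is 84 fewer, about 21% short.

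**2. Two-sided power at the planned size.** Normal approximation: Φ(d√(n/2) − 1.96).
- n = 310: 0.2 × √155 = 2.490, and Φ(0.530) = 70.2%. The noncentral t gives **70.1%**.
- n = 315 (450 × 0.70): 0.2 × √157.5 = 2.510, and Φ(0.550) = 70.9%. The noncentral t gives **70.8%**.

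**3. Effect detectable with 80% power at 310, two-sided.** (1.9600 + 0.8416) × √(2/310) = 2.8016 × 0.0803 = **0.225 SD**.

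**4. Attrition step.** 310 / 0.70 = 442.9, so 443 per group and 886 in total, rounded up to 900. This step is correct.

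**5. Does 20% equal 0.2?** The article gives nothing to convert one into the other, so the values below are assumptions chosen to show the range.
- *Relative difference in means.* d = 0.20 / CV, where CV = SD / mean. This equals 0.2 only when CV = 1.

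| Assumed CV | d | Two-sided n per group for 80% power (normal) | Two-sided power at 310 |
|---|---|---|---|
| 0.8 | 0.250 | 252 | 87% |
| 1.0 | 0.200 | 393 | 70% |
| 1.2 | 0.167 | 566 | 54% |
| 1.5 | 0.133 | 883 | 38% |

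- *Absolute difference of 20 percentage points.* For control rates from 10% to 60%, the two-sided requirement is 62 to 97 per group. None of these is near 310.
- *Relative difference of 20% in proportions.* 50% v 60% has Cohen's h = 0.201 and needs 305 per group one-sided or 388 two-sided. 55% v 66% needs 309 two-sided.

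So 310 follows directly from 0.2 with a one-sided test. Whether a 20% difference amounts to the same thing depends on figures the article does not give.

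**The case against.** The strongest reply is that the article never says two-sided. A reader might infer that 310 is an arithmetic mistake, or that the stated power is simply wrong by ten points. The text does not support that: for a one-sided 5% test 310 is exactly right, and a programme intended to raise activity might have been planned with a directional test. The shortfall exists only if testing is two-sided. What remains is that a one-sided level has to be declared, and it is not.

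A reader might also infer that 310 can arise only from a one-sided test. That is true only of a plain comparison of means at 0.2. The section does not name the test, and other two-sided routes exist. One is 55% v 66% (309 per group). Another is adjustment for a baseline value correlated at about 0.46 with the outcome: 393 × (1 − 0.46²) = 310. The planned repeated-measures and logistic analyses do not exclude these. But each needs an input that the article does not mention, whereas the one-sided match uses only the stated inputs.

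A third tempting inference is that the 20% difference is not what the trial was powered for. This is not shown. The two targets agree if the SD equals the mean, and nearly agree for 50% v 60%. What can be said is that the 20% is undefined and unlinked to 0.2. The table by CV shows sensitivity to an unknown, not a demonstrated loss of power.

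Finally, an article condenses a fuller protocol, and the sidedness may be recorded there. That is fair, but this paragraph makes a complete power claim with its own inputs, and on the ordinary reading those inputs do not yield the stated number.

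**Conclusion.** The point holds in conditional form. The 310 per group is the one-sided 5% answer for d = 0.2 and 80% power, and one-sided testing is not declared. If testing is two-sided, 394 per group would be needed. Power for 0.2 SD is then about 70% at 310 and about 71% at 315, and 80% power is available only for about 0.225 SD. If one-sided 5% was intended, the figure stands and only the declaration is missing. Separately, the 20% difference has no stated meaning in terms of the 0.2 used.

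These results assume a simple two-group comparison of means without baseline adjustment, and independent participants. The Recruitment and randomisation process section assigns suburbs, so any correlation within suburbs would lower the power further. That is a separate matter and is not counted here.

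**What to change.** Reword the Sample size determination paragraph, without enrolling more mothers:

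- State whether the 5% level is one-sided or two-sided.
- If two-sided, replace the 80% claim with either about 70% power for 0.2 SD or 80% power for about 0.225 SD, at 310 per group, and say that this is before any allowance for clustering.
- If one-sided 5% was intended, say so explicitly.
- Replace the 20% difference with 0.2 SD, or give the mean and SD (or the baseline rate) that make the two equal.

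The cost is one paragraph of rewording and, if testing is two-sided, a less favourable stated power. For comparison, keeping 80% two-sided power at 0.2 SD would take 394 / 0.70 = 563 per group, or 1,126 in total against 900. The restatement avoids that.

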### Data collection

Process data will be collected during the implementation of the intervention. The playgroup is a novel setting for the recruitment and delivery of health promotion interventions for mothers with young children. Therefore, the process evaluation will be a key component of the program's evaluation. This will be conducted with both the participants and the project staff, providing two perspectives on the program delivery and content.

Outcome data will be collected at baseline, six months and 12 months. At baseline control group participants will be hand delivered a self-completion questionnaire at the playgroup along with a self-addressed envelope and measuring tape to record waist and hip measurements. The intervention group will be provided all of the above and a pedometer to record the number of steps taken each day. At six months the control group participants will be hand delivered a self-completion questionnaire at the playgroup along with a self-addressed envelope. The intervention group will be provided all of the above and a pedometer to record the number of steps taken each day. At 12 months the control and intervention group participants will be posted a self-completion questionnaire with a self-addressed envelope.

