### Study aim

The REFRESH study aims to evaluate the effect of a six month physical activity and nutrition randomized controlled trial for mothers with young children attending playgroups in Perth, Western Australia (WA).

The REFRESH program will focus on behaviour change to meet the Australian physical activity guidelines, by encouraging increased in levels of vigorous, and moderate physical activity, the number of steps taken each day and muscle strength exercises [30,31]. The REFRESH program will also aim to encourage behaviour change to meet the Australian dietary guidelines (improve nutritional intake by increasing fruit, vegetable and fibre intake and decreasing fat and added sugar intake) [32].

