##### Delivery of face-to-face workshops

The intervention group participants will receive six workshop sessions over six months (one session a month). Each session will be conducted for 30 minutes by project staff during the playgroup session at the playgroup venue. Workshops will focus on enhancing knowledge, attitudes and skills to enable informed decision making about nutrition and physical activity behaviours (Table 1).

**Table 1 T1:** REFRESH Intervention

Session (Week)	Session Details	Participant resources/interactive activities
1 (Week 1)	1. Introduction to Refresh Program 2. Overview of healthy eating and being physically active 3. Focus nutrition: fruits, vegetables and water • Guidelines • Benefits/barriers/overcoming barriers	1. Resources: • Program booklet • Healthy recipe booklet • Session one information summary pamphlet 2. Interactive activity: • Determine participant program needs

2 (Week 5)	1. Focus behaviour change: • Stages of change • Goal setting: long and short term goals 2. Focus physical activity: aerobic • Guidelines • Benefits/barriers/overcoming barriers 3. Focus nutrition: five food groups and 'extra' foods • Guidelines • Benefits/barriers/overcoming barriers	1. Resources: • Pedometer • Family dinner and physical activity planner (fridge magnet) • 'Extra' food record sheet • Session two information summary pamphlet 2. Interactive activity: • Playgroup 10,000 steps per day challenge

3 (Week 9)	1. Focus behaviour change: • Review established short term goals • Set new short term goals 2. Focus physical activity: Muscle strength and flexibility exercises • Guidelines • Benefits/barriers/overcoming barriers	1. Resources: • Muscle strength and flexibility exercise card (fridge magnet) • Physical activity diary • Session three information summary pamphlet 2. Interactive activity: • Muscle strength and flexibility exercises • Integrated exercises "

4 (Week 13)	1. Focus behaviour change: • Review established short term goals • Set new short term goals 2. Focus nutrition: • Healthy eating messages • Menu planning • Food label reading • Making sense of nutritional claims	1. Resources: • Shopping list with healthy shopping tips • Comparing packaged food per 100 g (fridge magnet) • Session four information summary pamphlet 2. Interactive activity: • Reading packaged food labels • Developing a daily menu

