##### Delivery of home based component

The intervention group participants will receive home based resources at each of the face-to-face workshop sessions to support the content of the REFRESH program. The home based components will include a specially tailored program booklet, pedometer, menu planner fridge magnet, a shopping list with food label reading tips, a muscle strength and flexibility exercise chart fridge magnet, a physical activity diary and an 'extra' food record sheet. The workshops will offer an opportunity for these resources to be explained and for questions to be answered.

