### Outcome measures

The self-administered questionnaire will be comprised of instruments which have been previously validated and tested for reliability [50-52], and will undergo further reliability testing prior to its use at baseline.

Physical activity will be measured by The International Physical Activity Questionnaire (IPAQ) [53]. This instrument has been accepted as the physical activity measurement tool in many settings and is specifically designed for population-based prevalence studies. Muscle strength exercise assessment will be based on recommendations from the American Heart Association and Australian physical activity guidelines [54]. Physical activity knowledge will be assessed by a modified version of the American Adult's Knowledge of Exercise Questionnaire [55]. Dietary intake will be measured using a modified version of the Fat and Fibre Barometer [56]. The New South Wales Government questionnaire will be used to measure soft drinks, fruit juice and snack consumption [57]. Added sugar consumption will be assessed using the 2005 National Health Interview Survey [58]. Nutrition knowledge will be assessed by a modified version of the General Nutrition Knowledge Questionnaire [59].

Self-efficacy for nutrition and physical activity behaviours will be assessed. Nutrition and physical activity self-efficacy will be assessed using items from previously validated instruments [52]. Validated questions will also confirm participants' stages of change regarding fruit and vegetable consumption [60]. Social support for physical activity will be assessed based on items from the Sallis et al. instrument [51].

General physical and mental health will be measured by The Medical Outcomes Study Short-Form Health Survey (SF-8) [61]. SF-8 is a standard international generic instrument of health status. It comprises two summary scales - the physical component summary (PCS) score and the mental component summary (MCS) score.

Demographic characteristics will include gender, age, educational level, country of birth, marital status, socioeconomic status, financial status and co-morbidities. Anthropometric measures will include self-reported height and weight, waist and hip girth. A recent study has confirmed that self report measures are suitable for such studies when a correction factor is applied [62].

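### Pedometers go out with the baseline and six-month outcome packs in the intervention arm only, so steps have no randomised comparison and that arm's baseline activity report may not be cleanly pre-intervention

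*Protocol article*

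**What the plan says.** The second paragraph of the Data collection section of the Protocol article concerns outcome data and lists what each arm receives.

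- Baseline, control: "At baseline control group participants will be hand delivered a self-completion questionnaire at the playgroup along with a self-addressed envelope and measuring tape" for waist and hip girth.
- Six months, control: "At six months the control group participants will be hand delivered a self-completion questionnaire at the playgroup along with a self-addressed envelope".
- Baseline and six months, intervention: "The intervention group will be provided all of the above and a pedometer to record the number of steps taken each day". The sentence appears twice, once per time point.
- 12 months, both arms: "At 12 months the control and intervention group participants will be posted a self-completion questionnaire with a self-addressed envelope".

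The Control group section limits controls' contact with the project to completing the questionnaires.

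Other sections bear on how the pedometer should be understood. Study aim lists, among the activity behaviours to be increased, "the number of steps taken each day and muscle strength exercises". Delivery of home based component treats the device as part of the program: "The home based components will include a specially tailored program booklet, pedometer, menu planner fridge magnet". Table 1, session 2 (Week 5), lists it again, "Resources: • Pedometer • Family dinner and physical activity planner (fridge magnet"), next to a playgroup challenge of 10,000 steps per day. The Outcome measures section assigns physical activity to a questionnaire, "Physical activity will be measured by The International Physical Activity Questionnaire (IPAQ"), does not restrict it to one arm, and names no step-count measure.

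**The concern.** Two consequences follow from a pedometer that travels with the outcome packs of one arm only.

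First, step data will exist for the intervention group alone. A rise in steps from baseline to six months would be an uncontrolled before-after change, open to season, reactivity to being measured and selective return of records. Because steps are a stated target and are collected in the outcome-data paragraph, such a rise could easily be presented as an effect of the trial.

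Second, the outcome questionnaire may be completed under different conditions in the two arms. It is taken away, self-completed and returned by envelope. An intervention mother may already be wearing a device that the program itself uses to change behaviour, while a control mother is not. Physical activity is the quantity on which the trial is powered, and a baseline cannot be retaken once the packs are out.

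**Working it through.** No figure in the article underlies this point, and the remedy does not alter the sample size. The check sets the sections side by side and then traces where a measurement difference would enter the analysis.

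**1. Pack contents by arm (Data collection)**

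| Time point | Control | Intervention | Step data planned |
|---|---|---|---|
| Baseline | questionnaire, envelope, measuring tape | the same, plus pedometer | intervention only |
| Six months | questionnaire, envelope | the same, plus pedometer | intervention only |
| 12 months | questionnaire, envelope | the same | neither arm |

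Planned control step records: 0 of 450 at every time point. A between-arm difference in steps, or in change in steps, therefore cannot be estimated. No analysis plan can repair this, because the data are never collected.

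**2. Order of questionnaire and pedometer**

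The article does not say whether the questionnaire is completed before, during or after the pedometer is worn. Both are handed over together at baseline, so completion during wear is possible but not established.

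**3. Where a difference would enter**

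Write, in any unit of reported activity:

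- *a0* = shift in the intervention arm's baseline report caused by the baseline pedometer;
- *a6* = shift in its six-month report caused by the measurement pedometer, beyond what the program's own pedometer produces;
- *D6*, *D12* = true effects at six and 12 months.

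If the shifts are additive, the between-arm contrasts in change from baseline are:

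- six months: *D6* + *a6* − *a0*
- 12 months: *D12* − *a0*

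If the baseline is instead used as a covariate with slope *b*, *a0* is replaced by *b* × *a0*.

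Three things follow.

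- If *a0* = *a6*, the shifts cancel in the six-month change contrast but not at 12 months, where no measurement pedometer is supplied to either arm.
- If *a0* ≠ *a6*, the six-month contrast is off by *a6* − *a0*, which may have either sign.
- The sign of *a0* itself is not given. A pedometer might raise activity, or might make self-report more sober and lower it.

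The article gives no value for *a0* or *a6*, so neither the size nor the net direction can be computed.

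**4. Baseline pedometer against Table 1**

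Data collection places a pedometer in the baseline pack and another supply at six months, both for recording steps. Table 1 lists one as a program resource at Week 5. These could be separate measurement and program issues, or one device described in two places. The text does not settle which.

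**The case against.** The strongest reply is that steps are not a declared outcome. The Outcome measures section relies on the questionnaire, which both arms complete, and Study aim describes what the program encourages rather than its endpoints. A reader might infer that a trial endpoint has been lost, or that physical activity as a whole can no longer be compared. The documents support neither reading: the questionnaire comparison survives and the 12-month packs match. What remains is that Data collection gathers steps among outcome data without saying what they are for.

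A reader might also put a size on the bias. Assuming a reactivity of 0.05 to 0.10 SD, for example, would give 0.05/0.20 = 25% to 0.10/0.20 = 50% of the assumed effect size of 0.2. Nothing in the article anchors that range or excludes zero, it applies to a single time point, and it ignores possible cancellation. It should not be used. For the same reason one cannot assert that the baseline pedometer raises reported activity or pulls the contrast towards zero.

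At six months the objection goes further. The pedometer has been part of the program since Week 5, so activity it prompts by then is partly the effect under test. Only an additional prompt from the survey pack would be artefact.

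Lastly, a reader might call the baseline and Week 5 entries a contradiction. They can coexist, so this is an ambiguity.

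These replies narrow the point. They do not touch the absence of control step data or the unprotected order of questionnaire and pedometer at baseline.

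**Conclusion.** The point holds in a limited form. It is certain, and needs no assumption, that steps have no randomised comparison: intervention data are planned at baseline and six months, and control data at no time. It is possible, but not shown, that the intervention arm's baseline activity report is taken under self-monitoring and so is not a clean pre-intervention measure. That depends on mothers using the pedometer before they finish the questionnaire, which the article neither states nor prevents. The size and net direction of any bias are unknown. The main comparison of self-reported activity is exposed to an avoidable doubt rather than invalidated. The change is worth making before packs are issued, because the baseline cannot be recovered afterwards.

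**What to change.** 1. In Data collection, state that both arms complete and return the baseline questionnaire before any pedometer or other intervention material is issued.
2. State that the six-month measurement pedometer is issued only after the six-month questionnaire has been returned. This removes the extra prompt from the survey pack and leaves the program's own pedometer untouched.
3. State that steps are an uncontrolled within-arm process measure in the intervention group and will not be offered as evidence of a trial effect. If a between-arm claim on steps is wanted, collect them in the same way in both arms.
4. Say whether the baseline pedometer and the Week 5 pedometer in Table 1 are the same issue or separate ones, and align the two sections.

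Simply dropping the pedometer from the measurement packs is less attractive, because those packs are the only step collections documented at baseline and six months.

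The cost is a few sentences, a short delay in issuing pedometers, and giving up any between-arm claim on steps, or else the expense of pedometers for the control arm. The number of participants does not change.
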